**8.6 Community relations committee**

In preparation for the AIDSVAX B/E vaccine trial, BMA staff and IDUs established a Community Relations Committee (CRC).4 The CRC was formed in order to establish mechanisms to solicit and respond to community attitudes about study procedures, the reputation of the study in the community, and questions arising from participants or the general community. The BTSG and BMA staff will work with IDU community representatives to support and continue the work of the CRC. The CRC will be composed of IDUs, their family members, and representatives of local organizations and community sectors. The CRC will meet every 2 months.

The CRC will provide a forum for IDUs to express their views, clarify their needs, and contribute to the planning and conduct of the tenofovir study. During these meetings, the background, purpose, procedures, and measures taken to ensure participant confidentiality and privacy will be explained and discussed. Furthermore, the risks of participation, the voluntary nature of study participation, and informed consent will be reviewed. The outcomes of these discussions will be used to adjust and guide the execution of the study and to raise community involvement and support for the project.

**9. Study products**

Two study products will be used during the trial, tenofovir and placebo. Each tablet of tenofovir and placebo is film-coated to mask taste with lactose monohydrate, hydroxypropyl methylcellulose, titanium dioxide, triacetin, and FD&C Blue No. 2 aluminum lake for color.

Each product will be provided by Gilead Sciences, Inc. in white, 60 mL, high-density polyethylene bottles with white child-resistant caps. Each bottle will contain 30 tablets as well as a single silica gel canister to protect the product from humidity and fiber packing to protect the product during handling and shipping. Each bottle will be labeled with a randomization number, the protocol number, and expiration date.

**9.1 Tenofovir disoproxil fumarate (Tenofovir)**

**9.1.1 Chemical and pharmacokinetic properties**

Each tenofovir tablet provided by Gilead Sciences, Inc. contains 300 mg of tenofovir and the following inactive ingredients: microcrystalline cellulose, lactose monohydrate, pregelatinized starch, crocarmellose sodium, and magnesium stearate.

Tenofovir Disoproxil Fumarate (tenofovir), 9-[I-2-[[bis[[isopropoxycarbonyl)oxy] methoxy]phosphinyl]methoxy]propyl] adenine fumarate, is the oral pro-drug of the intravenous compound 9-[I-2-(phosphonomethoxy) propyl] adenine monohydrate. Tenofovir inhibits the activity of HIV reverse transcriptase by competing with the natural substrate deoxyadenosine 5’-triphosphate and, after incorporation into DNA, by DNA chain termination.

Tenofovir is rapidly absorbed with peak serum concentration reached between 0.5 and 1.5 hrs after oral dosing. Tenofovir is eliminated primarily by renal excretion and has an estimated terminal half-life of approximately 6-8 hours. In non-pregnant adults, the intracellular half-life for the disappearance of tenofovir, the active metabolite, is 12 to 15 hours in activated lymphocytes and 33 to 50 hours in resting lymphocytes.

Based on laboratory data using the HIV-1 IIIB strain in PBMCs, the concentration that inhibits 50% (IC50) of viral isolates is 0.18 µM or ~52 ng/mL. Equivalent antiviral activity has been shown against HIV-1 clade C and other HIV-1 non-B clade primary isolates (A, C, D, E, F, G, and group O).15

**9.1.2 Clinical trials**

The U.S. FDA approved Viread® (tenofovir) in October 2001 for use in combination with other antiretroviral therapeutic drugs for the treatment of HIV infection. Over 12,000 patients have participated in clinical trials or expanded access studies, and tenofovir has been shown to be generally safe, effective, and well tolerated. Ongoing clinical studies are examining tenofovir for use in new populations for new indications. Three studies are being conducted among HIV-infected pediatric populations to examine a suspension formulation. Other studies are assessing safety among adults with hepatitis B infection and for use as an intravaginal topical gel.

**9.1.3 Safety profile**

Tenofovir has almost exclusively been studied in HIV-infected adults, either as monotherapy for brief periods to assess safety or pharmacokinetics, or as a component of multi-drug combination therapy for treatment of HIV disease. The concomitant use of multiple antiretrovirals does not allow determination of the rate of toxicities we can expect when tenofovir is administered alone. However, data from placebo-controlled studies are available to examine the added risk of tenofovir in multidrug combination therapy.

Changes in bone growth and strength have been seen in study animals given tenofovir. It is unknown if tenofovir will cause bone abnormalities in humans. In studies of pregnant macaques given very high doses of tenofovir during pregnancy (6-12 times the dose to be used in this study), there was a reduction in bone mineralization in the macaque infants.16 However, in human tenofovir trials (in HIV-infected persons) to date, fracture rates have been lower in the tenofovir arm than in the placebo arm and nearly all fractures resulted from trauma.10 All reported bone fractures will be recorded as AEs, or if appropriate, SAEs and analyzed at interim and final DSMB safety analyses.

In a escalating dose study of tenofovir among 49 subjects, there were five grade III or IV adverse events deemed possibly or probably related to the study agent among 38 subjects who received tenofovir,18 and an equivalent proportion (1 of 11) of participants receiving placebo. The adverse events consisted of elevated serum creatinine kinase (n=5) and elevated liver transaminases (n=2). One tenofovir recipient developed peripheral neuropathy; this adverse event also occurred in one placebo recipient. All events resolved completely after discontinuation of the drug or placebo.

In a phase III, randomized, 600 antiretroviral-naïve participant, double-blind study of tenofovir + lamivudine + efavirenz compared to stavudine + lamivudine + efavirenz (903) the incidence of grade 3 or 4 adverse events and laboratory abnormalities was similar between the two groups.10 Through 96 weeks, nucleoside-related toxicities (e.g., peripheral neuropathy, pancreatitis, and lactic acidosis) were significantly lower in the tenofovir arm. Another phase III, randomized, double-blind trial (907) with 550 treatment-experienced participants, the incidence of clinical or laboratory adverse events was similar in tenofovir and placebo arms. (Table 1)

**Table 1. Study 907. Percentage of patients who experienced grade 3 or 4 events (occurring in >2 patients) regardless of relationship to study drug.**

| **Type of Event** | **Placebo**  **(N=182)**  **(Week 0-24)** | **Tenofovir**  **(N=368)**  **(Week 0-24)** |
| --- | --- | --- |
| **Clinical Adverse Event**  **Grade 3 or 4*** | | |
| Asthenia | <1 % | <1 % |
| Pain | <1 % | <1 % |
| Myalgia | 0 | <1 % |
| Abdominal pain | <1 % | <1 % |
| Nausea | 1 % | <1 % |
| Diarrhea | 2 % | <1 % |
| Pancreatitis | 0 | <1 % |
| Bacterial Infection | <1 % | <1 % |
| Cellulitis | <1 % | <1 % |
| Pneumonia | 0 | <1 % |
| Sinusitis | 1 % | <1 % |
| Renal Calculus | 0 | <1 % |
| Anxiety | 0 | <1 % |
| Depression | <1 % | <1 % |
| *Events causing permanent study drug discontinuation* | 2 % | 3 % |
| **Laboratory Abnormalities**  **Grade 3 or 4*** | | |
| Triglycerides | 13 % | 8 % |
| Creatine Kinase | 14 % | 7 % |
| Amylase | 7 % | 6 % |
| Urine Glucose | 3 % | 3 % |
| Serum Glucose | 4 % | 2 % |
| AST | 3 % | 3 % |
| ALT | 2 % | 2 % |
| Neutrophils | 1 % | <1 % |
| *Events causing permanent study drug discontinuation* | 2 % | 0 |

*see Appendix D for severity grading

Of special concern for the IDU population is the possibility of a drug-drug interaction between tenofovir and methadone. The pharmacodymamics (PD) and pharmacokinetics (PK) of tenofovir were examined in a study among 14 HIV-uninfected IDUs on stable doses of methadone. Following 14 days of directly observed therapy methadone PD and PK exposures were similar among tenofovir and placebo recipients.11

As of 30 April 2003, approximately 153,000 persons have taken tenofovir in clinical studies, expanded access programs, and in postmarketing settings in the United States, Europe, and Australia. Tenofovir has been generally well tolerated with few adverse events. It is reasonable to hypothesize that side effects and toxicities will be less in healthy, HIV-uninfected persons.

**9.2 Placebo**

Each placebo tablet provided by Gilead Sciences, Inc. contains the inactive ingredients listed above and denatonium benzoate to provide a bitter taste to match the tenofovir tablets.

**9.3 Drug accountability**

The study site~~s~~ will periodically receive a supply of study products, labeled with the randomization code. Study product will be stored in a limited access area that is securely locked and temperature controlled (range of 15 C – 30 C).

It has been demonstrated that tenofovir disoproxil fumarate tablets are stable at 25 degrees C and 60% relative humidity for up to 36 months; at 30 degrees C and 65% relative humidity for 18 months; and at 40 degrees C and 75% relative humidity for 6 months. Although tenofovir disoproxil fumarate tablets and placebo to match tenofovir disoproxil fumarate tablets should be stored at the clinical site(s) under controlled temperature and humidity conditions (25 degrees C; excursions not exceeding 15 degrees C to 30 degrees C) to ensure stability of the product, the aforementioned data does support dispensing a 30 day supply to study subjects who may keep their study drug in conditions that exceed these recommended storage conditions.

Strict inventory will be maintained on all study product received. Study product that has expired or been returned unused by participants will be destroyed as clinical waste in Thailand by incineration or burial.

**9.4 Adherence counseling**

Adherence counseling will be based on adherence research conducted among IDUs.13,19,20 The counseling session will be individualized and include the following:

- Basic education about study medications (e.g., dose and schedule, how tenofovir works, side effects and how to handle them, refills and storage, do’s and don’ts of taking study medication, etc.)
- Discussion of the participant’s beliefs and attitudes about taking tenofovir/placebo (e.g., concerns, expectations, fears)
- Encouragement about talking to study personnel about medications (e.g., what to tell study personnel about your medications, questions you might have and should feel free to ask, the need to be open even when adherence is poor so study procedures and adherence counseling can be improved)
- Identifying and solving barriers to adherence (e.g., scheduling and organizational skills, reminder devices, social support, disclosure)
- Discussion about reasons not to engage in pill-sharing and how to handle requests from friends and family to borrow doses

At each follow-up visit, study counselors will review the study participant’s self-report of adherence, discuss barriers to adhering to the daily dose of study medication, and help identify strategies for overcoming barriers.

**9.5 Adherence monitoring**

We will best be able to assess safety and efficacy of tenofovir in light of knowledge about medication use, so monitoring adherence is important. In addition to direct observed therapy for a subset of trial participants, four methods will be used to assess adherence:

- Self-report on interview: To encourage reporting of nonadherence, participants will be reminded that we understand taking all doses is difficult and that we need them to tell us about missed doses
- Pill counts: At each monthly study visit
- Medication diary: At each monthly study visit diaries will be reviewed and compared to pill count
- Tenofovir blood levels will be determined on unblinded specimens at the conclusion of phase III from:
  - All HIV seroconverters – serum from the first HIV positive visit and the last HIV negative visit for tenofovir recipients. Results will be compared to diaries and pill counts to assess adequacy of self-report to predict therapeutic blood levels around the time of seroconversion.
  - Specimens from 10% of all persons who received tenofovir and did not seroconvert will be randomly selected from the first quarterly visit and the quarterly visit before going off-drug. Results will be compared to diaries and pill counts to assess correspondence to self-reported adherence.

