**7. Trial design**

This is a phase II/III, randomized, double-blind, placebo-controlled study of the safety and efficacy of chemoprophylactic tenofovir, administered orally once daily to IDUs. The study will be conducted in Bangkok at 17 BMA Drug Treatment Clinics. Study participants will be randomized (1:1) to receive tenofovir 300 mg or placebo. Participants will be evaluated for adverse events and HIV seroconversion.

The primary goals of this study are to assess the safety and efficacy of daily tenofovir to prevent parenteral HIV infection among IDUs. Assessment of changes in HIV associated risk behaviors, adherence to study drug, and, among IDU who become HIV-infected during the trial, evaluation of HIV viral load set point, CD4 counts, genetic characterization of infecting HIV viruses, and antiretroviral resistance will also be done.

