**7.2 Secondary endpoints**

Changes in HIV associated risk behaviors will be measured by:

- Rates of reported injection drug use and injection drug use frequency during the trial
- Rates of reported needle sharing
- The number of unprotected sexual acts over the course of the trial
- Number of reported sexual partners over the course of the trial
- Proportional use of condoms during sexual intercourse

Medication adherence will be measured as:

- Rates, by interview and documentation on tenofovir adherence card, of participants taking at least six (86%) of seven daily doses of study drug each of the four weeks preceding the monthly study visit

Differences in virologic and immunologic responses to HIV infection among tenofovir and placebo recipients will be measured by:

- Plasma viral load, measured by quantitative RNA PCR, a predictor of clinical progression of HIV disease;14 CD4 cell counts will be measured by flow cytometry
- Rates and nature of HIV antiretroviral genotypic and phenotypic resistance will be measured
- Genetic characteristics of infecting HIV viruses including DNA sequence analysis and antibody binding studies will be conducted

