**10.3.1 Daily directly observed therapy (DOT)**

Participants will come to clinic each day and clinic staff will observe the participant swallow one tablet of tenofovir or placebo. Clinic staff will complete and sign the participant’s adherence card.

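### Serum tenofovir reflects roughly the last two days of dosing, so it cannot confirm or refute a monthly pill count, and the protocol text does not call for the last-dose time needed to interpret it

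*Protocol*

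**What the plan says.** Section 9.5 lists self-report, pill counts, medication diaries and tenofovir blood levels as adherence measures, alongside directly observed therapy (DOT) for a subset. Pill counts and diary review take place at each monthly visit. Blood levels are measured at the end of phase III in two groups:

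- **Non-seroconverters.** A random 10% of tenofovir recipients, with specimens from the first quarterly visit and from the last quarterly visit before stopping drug. The stated use is: "Results will be compared to diaries and pill counts to assess correspondence to self-reported adherence".
- **Tenofovir-arm seroconverters.** Specimens from the last negative and first positive visits. The stated use is to see whether self-report predicts therapeutic levels around seroconversion.

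Appendix C gives the matrix as serum and the assay as HPLC. Section 9.1.1 says that tenofovir "has an estimated terminal half-life of approximately 6-8 hours", with "peak serum concentration reached between 0.5 and 1.5 hrs after oral dosing". Its intracellular half-lives are longer, "12 to 15 hours in activated lymphocytes and 33 to 50 hours in resting lymphocytes", but no intracellular drug assay is listed.

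The adherence endpoint in section 7.2 is the rate of participants taking "at least six (86%) of seven daily doses of study drug each of the four weeks preceding the monthly study visit", measured by interview and adherence card. For the DOT subset, section 10.3.1 says: "Participants will come to clinic each day and clinic staff will observe the participant swallow one tablet of tenofovir or placebo".

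**The concern.** The check and the record it is set against look back over different periods. A serum level with a 6-8 hour half-life describes the last day or two, while a pill count gives one total for about four weeks.

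The mismatch can mislead in both directions. A tablet taken just before a scheduled visit can appear to confirm a full diary. One recent missed dose can appear to contradict a diary that is otherwise good.

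Timing adds a second difficulty. The level falls steeply over a dosing interval, and DOT participants take their tablet at the clinic, so a draw might come shortly before or shortly after a dose. Sections 9.5 and 10.3, Table 2 and Appendix C do not ask for the time of the last dose and do not place the draw relative to an observed dose. The assays are run at the end of phase III, so a dose time not written down at the draw cannot be recovered when the result is read.

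At stake is the reading of the adherence validation, which section 9.5 itself ties to interpreting safety and efficacy.

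**Working it through.** The protocol states no figure for how far back the serum level looks, so there is none to reproduce. The one calculation in the adherence definition is right: 6/7 = 85.7%, given as 86%.

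**Inputs**
- Half-life h = 6 to 8 hours (section 9.1.1).
- Dosing interval 24 hours: drug is "administered orally once daily to IDUs" (section 7).
- Interval covered by the diary and pill count: 28 days (monthly visits at 4-week spacing, section 10.3.2).
- Assumption, not from the protocol: first-order, one-compartment elimination. Absorption is ignored, which is tolerable at 2 hours or more after a dose given the stated time to peak.

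**Formulas.** Let r = 2^(-24/h) be the fraction of a dose left after 24 hours, and scale one dose to an initial level of 1. A daily taker's trough is r + r² + r³ + … = r/(1 - r). Then:

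- one tablet only, 24 hours before the draw, relative to that trough: r ÷ [r/(1 - r)] = 1 - r
- alternate-day dosing, last tablet 24 hours before: 1/(1 + r)
- every dose taken except the last one: r
- every dose taken except the last two: r²
- share of the trough from doses older than the last two: r²
- daily taker drawn 2 hours after a dose, relative to trough: 2^(22/h)

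**Results**

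| Quantity | h = 6 | h = 8 |
|---|---|---|
| r | 6.25% | 12.5% |
| One tablet 24 h before draw | 93.8% | 87.5% |
| Alternate-day, last tablet 24 h before | 94.1% | 88.9% |
| Missed only the last dose | 6.25% | 12.5% |
| Missed the last two doses | 0.4% | 1.6% |
| Share from doses older than the last two | 0.4% | 1.6% |
| Drawn 2 h after a dose ÷ trough | 12.7 | 6.7 |

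**Reading the table**
- One tablet in 28 days is 1/28 = 3.6% adherence, yet the serum level is within 6-13% of that of a daily taker drawn at the same time after a dose.
- Missing only the last of 28 doses is 27/28 = 96.4% adherence and meets the section 7.2 rule, yet the serum level is 6-13% of the usual trough.
- For a perfectly adherent participant, drawing 2 hours rather than 24 hours after a dose changes the level about 7- to 13-fold. Without the dose time, this variation cannot be separated from missed doses.

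**A longer-lived marker, for comparison.** With the intracellular half-lives in section 9.1.1, one tablet 24 hours earlier gives 1 - r = 75% to 67% of the daily-dosing level (12-15 hours) or 40% to 28% (33-50 hours). Only the resting-lymphocyte range clearly separates one tablet from daily use.

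**Scale.** With 2,400 enrolled 1:1, 10% of the tenofovir arm is about 0.10 × 1,200 = 120 people, each with two specimens.

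**The case against.** The strongest reply is that serum is one check among several and is not asked to carry four weeks alone. Much of this stands:

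- Pill counts and witnessed DOT doses do not rest on self-report either. Pill counts cover the interval that serum misses. A reader might infer that serum is the only objective check, but section 9.5 does not support that.
- No sentence says that serum validates four-week adherence. The text says only that results will be compared with diaries and pill counts. A diary can be read over its last days, but a pill count is a total for the interval and cannot.
- Each sampled person contributes two specimens, not one.
- The seroconverter comparison asks about levels around seroconversion, a short-window question that suits serum.
- Someone taking 1 tablet in 28 would also have to falsify the diary and dispose of about 27 tablets to pass the pill count. The 88-94% result describes the blood test alone.
- The check still works one way: a very low level contradicts a diary that shows doses taken in the last day or two.
- Table 2 and Appendix C would not list form fields, and the questionnaires and case report forms are not shown. The protocol text does not call for dose time, but that does not prove none is collected.

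A reader might also infer that efficacy would be judged against an inflated adherence figure. The documents do not support that. The primary analysis is by intention to treat (sections 13.7 and 13.9), the adherence endpoint uses interview and card (section 7.2), nothing rescales it by serum, and the assays come too late for the interim adherence-adjusted analyses in section 14.2.

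The reply does not remove the mismatch itself. The matrix and the records it is compared with are fixed in the protocol, and leaving the choice of diary days and cut-offs to an analysis plan would not supply a missing dose time.

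**Conclusion.** The point holds in a limited form. On the protocol's own half-life, serum informs about roughly the last two days of dosing. It can contradict a recent diary entry but cannot confirm or refute a monthly pill count. The level is hard to interpret even for those two days unless the time since the last dose is known.

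The percentages rest on one-compartment decay at 6-8 hours and on comparison at the same time after a dose. The protocol gives no concentration cut-off or assay limit, so how often a result would mislead cannot be calculated.

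The effect is confined to a supplementary validation, mainly the non-seroconverter comparison. This is a cheap improvement to an adherence check and does not threaten the trial's primary conclusion.

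**What to change.** In section 9.5 and the blood-collection procedures:

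1. Record the date and time of the last dose at each month 1, month 2 and quarterly draw. For DOT participants, also record whether the draw came before or after that day's observed dose.
2. Compare the serum level with diary or DOT-card entries for about the preceding 48 hours, judged against time since dose.
3. State that agreement does not validate adherence, or the pill count, over the whole interval between visits.

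The seroconverter comparison needs only the dose-time record.

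The cost is an addition to the blood-collection form and a revised sentence or two. The downside is a narrower validation claim: about the last two days, not the month. Nothing in dosing or clinical management changes.

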**9.6 Study drug interruption**

The study drug may be temporarily interrupted if the participant runs out of study drug because of a missed visit or the physician stops study drug to allow resolution of a transient adverse event. In such cases, an HIV test will be done to confirm the participant is HIV-uninfected before the participant resumes study drug.

